## **MATERIAL AND METHODS**

### **PATIENTS**

Total number of patients to be studied will be 60.

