### **Withdrawal from study**

1. Refuse further participation (withdrawal of informed consent).
2. Concomitant disease or exacerbation of background disease that may be unsafe for the patient to continue in the study (considered as an adverse event).
3. Protocol deviation that would prevent further participation in the study
4. Lost to follow-up.

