### **STUDY METHOD**

This will be an open label, prospective, randomized, two arm study to be conducted in renal transplant recipients who have undergone renal transplant >2 months prior to enrollment. Renal transplant recipients who had undergone live donor renal transplantation and are on CNI based maintenance regimen will be screened for inclusion and exclusion criteria. Informed consent will be taken after explaining the objectives and procedures of the trial from all the patients who agree to participate in the study. Subjects who satisfy all inclusion and exclusion criteria will either continue with existing CNI regimen or converted from CNI based regimen to sirolimus with CNI withdrawal.

At baseline patient's past, family, medical, transplant and medication history will be enquired and relevant findings will be recorded in the CRF. Patient's general and physical findings will be recorded. Baseline laboratory investigations including CBC, electrolytes, fasting blood sugar, renal profile, SGOT, SGPT, Lipid profile, urine analysis and 24 hrs urine test for urine proteins will be done and recorded. Baseline and subsequent GFR will be calculated by MDRD method. CNI dose and blood levels of all the patients will be recorded at baseline. Subsequently the patients will be randomized either to CNI group who will continue with existing dose or to Sirolimus group. Patients allocated to Sirolimus group, will be initiated

with a loading dose of 6mg for 2 days and later the dose will be adjusted to achieve a blood level of 8-15ng/ml. The CNIs in sirolimus group will be discontinued 12 hrs prior to initiating Sirolimus. Later, in CNI or sirolimus group the dose of individual drugs will be titrated as per target blood level and clinical response. Concomitant immunosuppressants like Mycophenolate mofetil (MMF) and steroids will be continued as per the clinical practice. All the drugs for any pre-existing or co-existing illness will be allowed unless those drugs are contraindicated. All the subjects will be assessed at regular intervals and at the end of study period of 6 months. Relevant laboratory investigations will be done at defined intervals and all the investigations done at baseline will be repeated at the end of study period.

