FoxP3+ T regulatory cell population will be analyzed at baseline, and at 1, 3 and 6 months after enrolment. By flowcytometry using anti-human allophycocyanin (APC) conjugated-CD4 antibodies, phycoerythrin (PE)-Cy7 conjugated-CD25 antibodies (BD Biosciences) and Alexa-fluor 488 conjugated-FoxP3 antibodies (BD Biosciences) on BD FACS Aria II (BD Biosciences). A total of 20000 events will be acquired, and CD25+ FoxP3+T cells will be counted using FACS DIVA 6.0.

1: 1 randomization will be done with the help of a computer generated random number table, and allocation concealment will be achieved by opaque sequentially numbered sealed envelopes. The response of the patient to the therapy will be in terms of renal function assessment. The primary analysis will be two-sided independent sample t-test for difference of means for GFR estimation by MDRD method.

A sample size of at least 25 patients per treatment arm will provide at least 80% power based on the assumption of an effect size (difference of GFR estimates between two treatment arms) of 8 mL/min and S.D. as 10 mL/min

The secondary endpoints will be:

- Acute rejection
- Patient and graft survival at 6 months,
- Incidences of hyperlipidemia, NODM, hypertension and infectious complications
- Regulatory T-cell population

All patients will be followed up at 15, 30, 60, 120 and 180 days. All investigations required to determine the primary and secondary end points will be performed. Sirolimus levels will be determined at 5, 12, 30, 60 and 120 days in patients randomized to sirolimus arm whereas those on tacrolimus will have measurements at 30, 60 and 120 days.

The target trough levels are as follows:

- Sirolimus: 8-15ng/ml
- Tacrolimus: 8-10 ng/ml upto mo 3, 6-8 ng/ml thereafter
- Cyclosporine: 200-300 ng/ml upto mo 3, 150-250 ng/ml thereafter

All unexplained episodes of graft dysfunction will be investigated by biopsy. Acute rejection will be treated as per standard protocol.

Variables will be presented as mean  $\pm$  SD and categorical variables as percentages. Appropriate statistical studies will be used for analysis of results. Two-tailed P-value  $<0.05$  will be considered significant.

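### The primary t-test uses one GFR per patient and leaves out the scheduled day-120 GFR, at a modest cost in power and with room for bias if loss is selective

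*Protocol*

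**What the plan says.** The Protocol, under STUDY METHOD, names the primary analysis: "The primary analysis will be two-sided independent sample t-test for difference of means for GFR estimation by MDRD method". It ties the test to no visit and gives it no baseline term and no repeated-measures structure. Significance is judged by a "Two-tailed P-value" below 0.05.

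GFR is measured more than once: "Baseline and subsequent GFR will be calculated by MDRD method". The same section lists the contacts: "All patients will be followed up at 15, 30, 60, 120 and 180 days". The STUDY VISIT PLAN is narrower. It marks serum creatinine, on which MDRD GFR depends, at visit 0, day 120 and day 180, and puts dashes at visits 1 to 3.

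On numbers, PATIENTS says "Total number of patients to be studied will be 60". STUDY METHOD says "A sample size of at least 25 patients per treatment arm will provide at least 80% power", assuming a difference of "8 mL/min and S.D. as 10 mL/min". No dropout rate is given. Withdrawal from study foresees consent withdrawal, unsafe concomitant disease, protocol deviation and "Lost to follow-up".

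**The concern.** The choice of test is stated, so this is not a detail left open for a later document. A two-sample t-test has no place for a second post-randomisation value. A patient who reaches day 120 and then leaves has a GFR that should say a good deal about the unseen day-180 value, and the named analysis does not use it.

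Two things are at stake. One is precision. The other is validity: a t-test on the patients who remain is unbiased only if loss is unrelated to GFR, or related in a way that cancels between arms. Here one arm changes drug and the other stays on its existing regimen, patients and staff know which is which, and the literature review in the Protocol describes a distinct side-effect burden for sirolimus with MMF. Loss that is unequal and related to health is therefore plausible, though not established.

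**Working it through.** **Inputs from the Protocol:** difference 8 and SD 10 mL/min, two-sided 0.05, at least 25 per arm (STUDY METHOD); 60 enrolled 1:1, so 30 per arm (PATIENTS, STUDY METHOD); creatinine at baseline, day 120 and day 180 (STUDY VISIT PLAN).

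**Assumptions, not in the Protocol:** correlation r between day-120 and day-180 GFR of 0.5 to 0.9, the loss rate, the timing of loss and the pattern of loss.

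**1. The plan's own figure.** Normal approximation: n = 2 × (1.960 + 0.842)² × 10²/8² = 24.5, rounded up to 25 per arm, with power 80.7%. The exact noncentral t gives 79.1% at 25 per arm. The stated figure reproduces.

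**2. Power of the t-test when only patients with the analysed value count** (30 per arm, noncentral t):

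| Loss | n per arm | Power |
|---|---|---|
| 0% | 30 | 86.1% |
| 10% | 27 | 82.2% |
| 15% | 25.5 | 80.0% |
| 16.7% | 25 | 79.1% |
| 20% | 24 | 77.4% |
| 30% | 21 | 71.6% |

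**3. Power when day 120 is used.** Let p180 and p120 be the proportions with a GFR at each visit. If loss is unrelated to GFR, the effective n per arm is 30 / [(1 − r²)/p180 + r²/p120].

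At one-sixth loss, p180 = 25/30 = 0.833.

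- Every lost patient has a day-120 value (p120 = 1), r = 0.7: 30 / (0.51/0.833 + 0.49) = 30/1.102 = 27.2, power 82.6%.
- Same, r = 0.85: 30 / (0.2775/0.833 + 0.7225) = 28.4, power 84.2%.
- Same, r = 0.5 and 0.9: power 80.9% and 84.8%.
- Half of the lost patients have one (p120 = 0.917), r = 0.5 to 0.9: power 80.1% to 82.2%.
- None has one: power stays at 79.1%.

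Against 79.1%, the gain is 1 to 3 points if half are seen at day 120. If all are seen, it is about 2 to 5 points for r up to 0.85, and just under 6 at r = 0.9.

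**4. Bias, simple form.** If a fraction d of one arm is lost and those patients average x mL/min below the arm's remaining patients, the observed mean of that arm is too high by d × x. For d = 0.10 to 0.20 and x = 5 to 15, this is 0.10 × 5 = 0.5 up to 0.20 × 15 = 3.0 mL/min, against a target difference of 8.

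**5. Bias, one adverse scenario.** Suppose a fraction f of the sirolimus arm leaves after day 120, each patient in the lowest 2f of day-120 GFR leaving with probability one half, while controls are lost at random. The t-test bias is r × 10 × f × m/(1 − f), where m is the distance in SDs of the lowest 2f group below the mean.

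- f = 0.17, m = 1.078, r = 0.7: 7 × 0.17 × 1.078/0.83 = 1.5 mL/min.
- f = 0.25, m = 0.798, r = 0.85: 8.5 × 0.25 × 0.798/0.75 = 2.3 mL/min.

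Simulation of this setting, with 5 to 17% random control loss, gives a t-test bias of 1.6 to 2.3 mL/min and rejection of a true null in about 9 to 13% of trials. A likelihood estimate using day 120 has bias below 0.1 mL/min.

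**6. Varying that scenario** (r = 0.8):

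- 17% loss, equally selective in both arms: t-test bias about 0, false-positive rate 4.9%.
- 5% loss per arm, selective in sirolimus only: bias 0.7 mL/min, false-positive rate about 6%.
- One-arm selective loss, half of it before day 120: the likelihood estimate using day 120 keeps about 0.7 to 1.0 mL/min of bias. At 17% loss per arm the figures are 0.8 for the likelihood estimate and 1.8 for the t-test.

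**The case against.** The strongest reply is that the Protocol never says lost patients are excluded. It gives no primary time point, analysis population or missing-data rule. A t-test can be run on imputed values, and such rules commonly sit in a statistical analysis plan, which may exist but is not at hand. A t-test is also valid in a randomised two-arm trial, matches the sample-size calculation, and agrees with the alternative when nobody is lost. All of that stands. A reader might infer that patients lost before day 180 are dropped by rule; the documents do not support this. What survives is narrower: the named test itself uses no intermediate GFR.

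Second, a reader might infer from the list of five follow-up days that five GFRs per patient are already collected. The visit plan supports only day 120 and day 180, so this objection also stands. Whether days 15, 30 and 60 yield a GFR depends on reconciling text and table.

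Third, the figures depend on the scenario. The larger power gains need every lost patient to have been seen at day 120. The inflated false-positive rate needs selective loss in one arm only. Equal selective loss in both arms produces neither bias nor inflation. This limits how firmly the size can be stated, but does not remove the possibility.

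**Conclusion.** The point holds in a limited form. The Protocol commits to a test that leaves at least one scheduled post-randomisation GFR unused, although it foresees withdrawal and loss.

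The power cost is modest: about 1 to 5 points at one-sixth loss, and nothing for patients lost before any post-randomisation GFR. It would be wrong to conclude that the stated 80% fails, because the ten patients enrolled beyond the required 50 keep the t-test near 80% up to about 15% loss.

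Possible bias is the better reason to change. An error of 0.5 to 3.0 mL/min against a target of 8 is conceivable, but only under assumed loss rates, GFR deficits and a difference between arms. None of these comes from the documents, so an inflated false-positive rate is a risk and not a demonstrated property of the plan. Day 180 as the analysed visit is likewise an inference from the 6-month study period.

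**What to change.** Replace the primary-analysis sentence with wording such as: *MDRD GFR will be analysed with a likelihood-based repeated-measures model covering baseline and every later visit at which creatinine is measured (at least days 120 and 180), with terms for arm, visit and arm-by-visit, baseline means constrained equal between arms, and an unstructured within-patient covariance. Everyone randomised is analysed in the assigned arm. The primary estimate is the arm difference at day 180, tested at the two-sided 5% level. A t-test at day 180 is supportive.*

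Baseline GFR as a covariate is a simpler alternative. However, a patient with no post-randomisation GFR then still falls out, whereas treating baseline as a response keeps that patient in the model.

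Also reconcile the follow-up list in STUDY METHOD with the STUDY VISIT PLAN, so that it is clear whether days 15, 30 and 60 yield a GFR.

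The cost is a few lines of text and a slightly more complex analysis, with no added patients. On the visit plan as it stands, no visits or tests are added either. The model relies on loss being explained by the observed GFRs. That is a weaker assumption than the t-test on remaining patients needs, but it is still an assumption. For patients lost before day 120, only baseline GFR can carry that information, so some bias may remain.

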**Support:**

The study drugs (sirolimus, tacrolimus and cyclosporine) will be provided by Biocon India, Bangalore.

## **STUDY VISIT PLAN**

| Visit                                                                                                                                                                                             | 0 | 1            | 2            | 3        | 4         | 5         |
|----------------------------------------------------------------------------------------------------------------------------------------------------------------------------------------------------------|----------|---------------------|---------------------|-----------------|------------------|------------------|
| Days                                                                                                                                                                                              |          | 0 - 14
(± 2days) | 15- 30
(± 2days) | 60
(± 7days) | 120
(± 7days) | 180
(± 7days) |
| Informed consent                                                                                                                                                                                  | X        |                     |                     |                 |                  |                  |
| Medical/ Transplant history                                                                                                                                                                       | X        |                     |                     |                 |                  |                  |
| General exam                                                                                                                                                                                      | X        |                     |                     |                 |                  |                  |
| Physical exam                                                                                                                                                                                     | X        |                     |                     |                 |                  |                  |
| Vital Parameters
(PR, BP, Fluid Intake and Urine output)                                                                                                                                      | X        | X                   | X                   | X               | X                | X                |
| Blood tests
CBC, Serum creatinine, Blood urea, electrolytes, Blood sugar, lipid profile, SGOT, SGPT, Urine for routine analysis, 24hrs urine for protein and Urine protein to creatinine ratio | X        | -----               | -----               | -----           | X                | X                |
| Therapeutic drug monitoring                                                                                                                                                                       |          |                     |                     |                 |                  |                  |
| i. Rapacan group                                                                                                                                                                                  | ----     | X                   | X                   | X               | X                | X                |
| ii. CNI Group                                                                                                                                                                                     | ----     | -----               | -----               | X               | X                | X                |
| Dose titration of                                                                                                                                                                                 |          |                     |                     |                 |                  |                  |
| i. Rapacan                                                                                                                                                                                        |          | X                   | X                   | X               | X                | X                |
| ii. CNI's                                                                                                                                                                                         |          | X                   | X                   | X               | X                | X                |
| Dose adjusts. Of concomitant drugs                                                                                                                                                                |          | X                   | X                   | X               | X                | X                |
| Recording of adverse effects                                                                                                                                                                      |          | X                   | X                   | X               | X                | X                |

